## 7.2 Inclusion Criteria

Elderly who are enrolled in the primary objective community study are also eligible to join the secondary objective 2.2 immunogenicity study and vice versa. The two studies are not required to be mutually exclusive.

For primary objectives, inclusion criteria include:

- Both males and females aged 65 years old or more;
- Non-institutionalized;
- Regular resident of That Phanom or Plapak Province (defined as being regular resident since Songkran 2014)
- Must be able to communicate adequately (able to see, hear and understand questions, and respond appropriately)

For secondary objective 2.2 (immunogenicity)

- In addition to the primary objectives' inclusion criteria, patient must present at the health facility requesting vaccination against influenza (so we can obtain baseline HAI titer).

For secondary objective 2.1 (functional status)

- Same as the primary objectives' inclusion criteria

For primary objective 1.3 (COPD exacerbations)

- In addition to the primary objectives' inclusion criteria, participant must be diagnosed with COPD

For secondary objective 2.3 (RSV incidence)

- Same as the primary objectives' inclusion criteria

### **7.3 Exclusion Criteria**

For primary objectives exclusion criteria include:

- Elderly with body disabilities that may have impact on self- nasal swab or telephone interview (i.e. elderly with stroke)
- Elderly with history of tumor in the nose or nearby areas
- Elderly with history of bleeding order (i.e. hemophilia)
- Elderly who often gets nosebleeds
- Any elderly with an acute medical condition or illness that could not participate in the study

For secondary objective 2.2 (immunogenicity)

- In addition to the primary objectives' exclusion criteria, any participant who has already been vaccinated with an influenza vaccine in 2015
- Known allergy to influenza vaccine or to egg
- Any participant with any medical condition that could prevent them from having a blood draw

For secondary objective 2.1 (functional status)

- Same as the primary objectives' exclusion criteria

For primary objective 1.3 (COPD exacerbations)

- Same as the primary objectives' exclusion criteria

For secondary objective 2.3 (RSV incidence)

- Same as the primary objectives' exclusion criteria

## **7.4 Discontinuation Criteria**

Participants in the community study, who choose to withdraw from the study, move permanently outside of the selected sub-district during the study or die during the study period will be considered discontinued. The study will be terminated if any major event results in the inability to contact majority of study participants or to collect adequate data and keep the data safe.

## **7.5 Methodology**

### **7.5.1 For primary objectives and secondary objectives 2.1, 2.3**

A list of all persons aged 65 years and older will be obtained for all villages in the selected That Phanom and Plapak districts. This list will be constructed by carefully surveying each participating village by health volunteers to get an accurate up-to-date listing of each elderly resident's name, address and age (as listed on their Identification card). Residents will be ordered and sorted in this order: district, sub-district, village, 5-year age band and systematically sampled proportionately using a sampling interval calculated from the total number of residents and the desired sample size, with a random start. A health volunteer and study team member will be paired together to approach their randomly assigned households every day to complete consent and enrollment. Health volunteers will be trained to seek consent for the study and explain the study methods to the participants. The study team will be trained on enrolling participants once they have consented by issuing a standardized baseline study questionnaire to each participant who consents to enrollment. Every participant that enrolls will receive a unique identification number which will be used in place of any identifying information in the central database. Consent and enrollment questionnaires with the elderly will take place in their homes and will take approximately 30 minutes to administer. Afterwards, the trained study staff member will show a standardized video to all enrolled participants on how to self-swab and store the swab correctly as shown in Appendix 5a.

All participants will be provided a self-swabbing kit from the study team that includes Dacron swabs and test tubes with transport media (TM) which are already labeled with the participants' hospital number, along with written instructions. Participants will be asked to take one nasal self-swab, and to place it in the refrigerator in a separate test tube filled with 1-3ml of TM. Participants will then be asked to describe the procedure to ensure they understand the full technique and will be guided appropriately. Participants will be given a study card with their study ID number and assigned health volunteer's telephone number. Participants who experience an ARI, defined as new onset of cough or worsening of chronic cough, will be asked to take a self-swab as soon as possible and then to call their assigned health volunteer to make an appointment to have their swab collected and answer some questions for the ARI/SARI Episode Questionnaire at the time of the appointment (which will be within 24 hours). The assigned health volunteer will bring an ice box and new Dacron self-swab kit to the sick participant's home, and the specimen will be transported in the ice box by the health volunteer to the sub-district health center for temporary storage. Health volunteers will also conduct the Functional Status Questionnaire three to four weeks after the onset of a participant's ARI or SARI and the Outcomes and Costs of ARI Questionnaire 1 week after the participant recovers which will be monitored through the weekly calls and by the study team. If a participant is very ill due to an ARI and needs assistance in taking a nasal self-swab, they can ask their assigned health volunteer for help in obtaining the specimen. Health volunteers will also be trained to contact their assigned participants weekly to identify ARI events that they have not been notified of already and to take a weekly questionnaire. They will attempt three contacts, by phone or in person, at different times of the day before considering the participant to have missed the week. In the case of an ARI event, participants who have not yet taken a self-swab will be asked to self-swab immediately.

For any participant that does not have a phone or for participants who have a phone without a working signal, we will have the health volunteer follow-up with them on a weekly basis by making household visits instead of a weekly call and rely on this method for collection of all data. If a participant without a working phone develops an ARI or SARI during the week and is able to send someone to the health volunteer to let them know, the health volunteer can also follow-up with the patient using the electronic ARI/SARI Episode Questionnaire, but this is not mandatory for participants without a working phone. If the participant needs to get in touch

with the researcher, the health volunteer will be trained to use their phone to call the researcher for them. When health volunteers transport the specimens to the sub-district health center/district hospital, they will place them inside a refrigerator with a controlled temperature of 2-8°C. Research nurses at the district hospital will be trained to transport the swabs from the refrigerator into the liquid nitrogen tank once a day to keep the specimens below -70°C until transported to NIH.

One research nurse from each health center will be responsible for the enrolled participants within their sub-district. In the event that a participant becomes very ill and goes to the hospital or sub-district health center for treatment of an ARI or SARI, the research nurse at the sub-district health center or district hospital will collect a nasopharyngeal swab from the participant and store it in a refrigerator as outlined in appendix 5a. They will administer the ARI/SARI questionnaire (for health centers) and call the study team to notify them about the participant's visit. The study team will inform the participant's assigned health volunteer so the health volunteer can monitor the participant and take the Functional Status Questionnaire and the Outcomes and Costs of ARI Questionnaire after the participant recovers at the appropriate time period. The nasopharyngeal swabs will also be placed inside a liquid nitrogen tank at the sub-district health centers and district hospitals once a day by trained study team personnel. The nurses at the district hospitals will also collect a nasopharyngeal swab for all participants with COPD who come to the COPD clinic due to an exacerbation.

The nasal and nasopharyngeal swabs will be picked up from all health centers involved in the study on a weekly basis by hired study staff and transported to the NIH laboratory in Nonthaburi in a liquid nitrogen tank for testing. They will be tested by rRT-PCR for the presence of ribonuclease P (RNase P). RNase P is commonly used as an internal control in PCR to indicate the presence of human cells. rRT-PCR involves using the nasal swab samples placed inside VTM and mixing them with a buffer before being incubated at 70 degrees Celsius. Then the RNA is extracted from the mixture using Nucleospin RNA virus. The RNA is eventually mixed with a diluted solution of primers and probes and placed onto a PRC plate or in a PCR tube with a mixture of reagents. This PCR tube or plate is then placed inside a Realtime PCR machine at different temperatures and for various time periods. The results are converted to cycle thresholds (4). The cycle threshold number in rRT-PCR indicates how fast the target is detected and tends to correlate with the amount of the target detected. We will consider samples with

cycle thresholds  $<37$  for RNase P to be adequate (4). We will also record the cycle threshold for additional classifications. The results of the PCR testing (whether the participant has influenza or RSV) will be added to the centralized database in Nonthaburi.

As mentioned above, health volunteers will be trained to make weekly visits/calls to the homes of the participants and answer a short electronic questionnaire case report form (CRF) accompanying the visit/call about each participant's incidence of ARI which will be collected on a hand held computer and synced into a centralized data base at That Phanom and Plapak district hospitals at least once a week.. They will also be asked to assess the elderly participant's functional status and cost of having an ARI after any participant recovers from an ARI/SARI at the specific time period; information will be recorded onto a questionnaire CRF on a hand-held computer as well. CRFs will have each participant's unique identification number input and the health volunteer will transfer data regularly to the district hospitals and the centralized database.

All persons with COPD are required to report to the district hospital's COPD clinic if they are experiencing exacerbations and for check-up. If a participant has COPD, the participant's medical records will be checked by a research nurse at each district hospital to record when and the number of times the participant visited a health center to seek care for a COPD exacerbation onto an electronic questionnaire CRF. We will know if the COPD exacerbation was laboratory-confirmed influenza-associated through results of the nasopharyngeal swab testing during their COPD clinic appointment at the same time period and whether patient was experiencing an ARI or SARI.

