Laboratory testing of nasal and nasopharyngeal swabs: Nasal self-swabs from participants will be stored in transport media (TM) and immediately transported with ice packs to the sub-district health center by a health volunteer and placed into a refrigerator monitored to be between 2 to  $8^{\circ}\text{C}$  for a maximum of 24 hours. From there, the specimens will be transported to the district hospital in ice packs where they will be stored in liquid nitrogen tanks within 24 hours. Nasopharyngeal swabs taken by nurses will also be stored at the local health center in a regulated refrigerator for a maximum of 24 hours and transported to the district hospital with ice packs to be stored in liquid nitrogen tanks. All respiratory specimens will then be transported to the MOPH National Institute of Health (NIH) laboratory in Nonthaburi in liquid nitrogen tanks where they will be tested using rRT-PCR for influenza and RSV using protocols developed by CDC (4). If specimens will not be tested immediately upon arrival at the laboratory, they will be stored below  $-70^{\circ}\text{C}$  until tested.

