**For the study team in the Community:**

1. Show a video demonstrating the above technique to the participant step-by-step without the materials which follow the below written instructions “How to take a nasal self-swab”
2. Ask the participant to demonstrate the technique for taking a nasal self-swab without the materials to show that they understand the technique
3. Instruct the participant to take a nasal self-swab when they have a new onset of cough or worsening of chronic cough
4. Instruct the patient to store their nasal swab test tube in the refrigerator
5. Then instruct patient to immediately call their assigned health volunteer to schedule a time for the swab to be picked-up within 24 hours
6. Write health volunteer’s telephone number for the patient on the written instruction sheet and let participant know that they can call the health volunteer if they have any concerns or need help.
7. Ask patient to verbally repeat steps 3 to 5 to demonstrate understanding

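### Responding to a reported illness is optional for participants without a working phone, although the protocol otherwise sets a 24-hour swab pick-up after a report

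*Protocol*

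**What the plan says.** Protocol Section 7.5.1 describes two routes.

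- **Participant who can call.** The participant self-swabs and phones the assigned volunteer, who makes an appointment. The swab is collected and the participant will "answer some questions for the ARI/SARI Episode Questionnaire at the time of the appointment (which will be within 24 hours". The community instructions in Appendix 5a have staff tell every participant to call and "schedule a time for the swab to be picked-up within 24 hours", with no exception for people who cannot call.
- **Participant with no phone or no signal.** The volunteer follows up by "making household visits instead of a weekly call and rely on this method for collection of all data". If the participant becomes ill during the week and "is able to send someone to the health volunteer to let them know", the volunteer "can also follow-up with the patient using the electronic ARI/SARI Episode Questionnaire, but this is not mandatory for participants without a working phone".

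At the weekly contact, form 4c asks about new illness in the past week. A new or worse cough with no swab yet taken leads to a swab and an episode questionnaire. Section 7.5.1 allows three contact attempts before a week counts as missed.

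The enrollment questionnaire (form 4b, items 72 to 74) records phone ownership and use. Section 7.9 gives age, co-morbidities and distance to a health facility as examples of adjustment variables.

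**The concern.** The primary outcome is laboratory-confirmed influenza ARI or SARI, compared by vaccination status. It depends on a swab being taken soon after onset and reaching cold storage in good condition. The exemption applies after the volunteer has already been told of an illness, so it is not explained by the volunteer's not knowing. It lets the speed of the response depend on phone access, a baseline characteristic.

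If later swabs or later collection lose true positives, detection will be lower among people without a working phone. If that group is also more or less often vaccinated than the rest, the loss will not fall equally on the two sides of the comparison, and the VE estimate will move.

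**Working it through.** The plan gives no figure for this point to reproduce. The check sets the rules side by side, derives the possible delay, and then illustrates the effect on VE.

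**1. The rules after an illness report**

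| | Can call | No working phone |
|---|---|---|
| Guaranteed response to a report | Appointment, pick-up and questionnaire within 24 hours | None before the next weekly visit |
| Source | Section 7.5.1; Appendix 5a | Section 7.5.1 |

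The exempting clause is loosely worded. What is not mandatory may be the volunteer's follow-up, which is the natural reading, or the participant's sending of word. On either reading only the weekly visit is assured.

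**2. Delay from report to guaranteed contact**

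Assumptions: visits are exactly 7 days apart, reports are uniform over the interval, and the volunteer never uses the option to come sooner. The wait is then Uniform(0, 7) days.

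- Maximum: 7 days, against 1 day for a participant who calls.
- Mean: 7/2 = 3.5 days.
- Share reached within 24 hours: 1/7 = 14%; share waiting longer: 6/7 = 86%.
- One missed week raises the maximum to about 14 days.

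These are worst-case values, because some volunteers will respond anyway.

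**3. Illustrative effect on VE**

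The true VE is taken as the 40% expected in Section 7.1.5, a rate ratio of 0.60. The documents give neither the share without a working phone (f) nor the proportion of positives lost among them (L), so both are assumed. Detection in a group is 1 − f × L, and

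observed VE = 1 − 0.60 × (detection in vaccinated) / (detection in unvaccinated).

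| f vaccinated | f unvaccinated | L | Detection, vaccinated | Detection, unvaccinated | Observed VE |
|---|---|---|---|---|---|
| 15% | 25% | 30% | 0.955 | 0.925 | 1 − 0.60 × 0.955/0.925 = 38.1% |
| 15% | 25% | 50% | 0.925 | 0.875 | 1 − 0.60 × 0.925/0.875 = 36.6% |
| 25% | 15% | 30% | 0.925 | 0.955 | 1 − 0.60 × 0.925/0.955 = 41.9% |
| 25% | 15% | 50% | 0.875 | 0.925 | 1 − 0.60 × 0.875/0.925 = 43.2% |

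If f is the same in both groups, the detection terms cancel and VE stays at 40%. They also cancel within each phone group if the loss there does not depend on vaccination: among people without a phone the ratio is 0.60 × (1 − L)/(1 − L) = 0.60. Adjustment for phone access would then remove this bias, but it would not recover the lost events.

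**The case against.** The strongest reply is that a backstop exists. Participants without a phone get a household visit every week, and that visit asks about illness and prompts a swab. Form 4d codes onset up to 7 days back for everyone, so a swab some days after onset is accepted across the cohort. Participants with phones who do not call are also found only at the weekly contact. This stands, and it narrows the point: no episode is dropped by design, and the two standards differ only for people who report between contacts.

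Three stronger readings are tempting, and the documents do not support them.

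- A reader might infer that the 24-hour limit in the laboratory text of Section 3.1.4 is breached. That limit covers refrigeration at the health center. The text does have the swab "immediately transported with ice packs to the sub-district health center by a health volunteer", but it sets no maximum time at home, where participants are told to refrigerate the tube. The conflict is with the pick-up limit in Section 7.5.1 and Appendix 5a.
- A reader might infer that help for the severely ill becomes optional. The exempting sentence concerns follow-up with the episode questionnaire. The offer of transport in Section 3.1.4 does not depend on having a phone, and nurses swab participants who present with a qualifying illness.
- A reader might infer that VE is biased in a known direction. The phone shares and detection losses above are assumed, and reversing the imbalance reverses the shift.

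It is also fair to say that the covariate list in Section 7.9 gives examples only, so not naming phone access there is no error. The faults are the exemption itself and its conflict with the 24-hour rule.

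**Conclusion.** The point holds in limited form. For participants without a working phone, the protocol guarantees only the weekly visit even after an illness has been reported, while elsewhere it sets a 24-hour appointment and pick-up after a report with no stated exception. The passages contradict each other and must be reconciled.

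The consequence is a possible delay of up to about 7 days in taking or collecting the swab, longer if a week is missed. Detection of the primary outcome may therefore depend on phone access. A bias in VE requires two further conditions that the documents leave open: that delay loses true positives, and that phone access differs by vaccination status. The illustrated shifts, from 40% to between 37% and 38% or to between 42% and 43%, show a modest effect of unknown sign; they are not estimates. The change is worth making because analysis cannot recover swabs that were collected too late.

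**What to change.** 1. In Section 7.5.1, delete the clause that makes follow-up non-mandatory for this group. State that any illness report the volunteer receives, by whatever route, leads to the same swab pick-up within 24 hours and to form 4d.
2. In Appendix 5a, add how a participant who cannot call should send word, so that the two texts agree.
3. Include phone access (form 4b items 72 and 74) as a covariate in the propensity and VE models. These items do not show whether a phone has a signal, and Section 7.5.1 treats no signal like no phone. The contact type on form 4c (in person or by phone) can supplement them.
4. Tabulate time from onset to swab by phone access, using form 4d items 6 to 9, which are already collected.

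The cost is extra travel by volunteers who already visit these homes weekly. The amount cannot be stated, because the number of participants without a working phone is not given. Participants who cannot send word will still depend on the weekly visit, and the change does not help them.

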### **For primary objective 1.2 (Direct and Indirect costs)**

When a participant becomes ill due to an ARI or SARI, we will train health volunteers to ask them about their costs associated with the infection with an electronic questionnaire CRF 1 week after recovering from their illness. If the participant went to a public health center or hospital, staff authorized by the hospital director will check their medical records to determine the cost of the visit. If the participant went to a private clinic, the standardized questionnaire will ask about the amount of money they and their insurance spent in order to treat/get treated for their illness including all laboratory and examination tests, clinician fees, hospital fees, medication fees. The questionnaire will also ask all participants regarding cost of over-the-

counter medications including herbal or traditional medicine costs, transportation fees, and questions to determine how much income their household lost due to missed work days of the elderly participant and of caregivers who take care of the participant to calculate indirect cost.

Records from the Provincial Medical Office and the National Health Services Office will be used to determine the cost of the vaccination campaign, which will be converted into a per capita cost per vaccinee. Data from the Provincial Medical Office will also be collected on average cost of outpatient visits for acute respiratory infection and inpatient admissions for pneumonia.

